### Withdrawal and replacement criteria for treatment

Every patient has the right to refuse further participation in the study at any time and without providing any reasons. A patient’s participation will be terminated immediately upon their request. The investigator should seek to obtain the reason and record this in the eCRF. This study is designed as an intention-to-treat (ITT) study.

### Safety assessment

Patient safety will be assessed at every visit until the end of treatment. They will be monitored for adverse events (AEs) using NCI-CTCAE V4.0 criteria. All AEs are to be documented in the eCRF. In cases of serious adverse events (SAEs), the event is also to be documented on the SAE form provided by the sponsor. The SAE management will be conducted by the Clinical Study Center. The processes are described in a separate SAE Manual. Annually, a development update safety report (DSUR) must be submitted to the competent authority (BfArM).

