## Methods and design

RiMINI is a monocentric exploratory pilot study on 60 patients with MHE as assessed by critical flicker frequency (CFF) analysis. Additionally, visual evoked potentials’ (VEP) testing, electroencephalography (EEG) and a psychometric test (NCT-A) will be carried out. The patients will be randomized to treatment either with rifaximin alone 550 mg twice daily (bid) continuously for a period of 3 months or to continuous treatment with 550 mg rifaximin bid in combination with lactulose 30–60 ml daily (to pass 2–3 semisoft stools/day) for 3 months. An esophagogastroduodenoscopy (EGD) will be performed at baseline, at the end of antibiotic treatment, as well as 6 and 12 weeks after the end of treatment to obtain gastric and duodenal biopsies and aspirates will be taken. The samples will be analyzed for their specific bacterial taxae by applying next generation sequencing (NGS) after ribonucleic acid (RNA) isolation. Additionally, stool samples will be taken at the same time points. Prevalence of *Helicobacter pylori*, which is the predominant gastric microbe, will be assessed by histology, rapid urease test and serology at study entry. For clinical assessment, quantification of MHE and therapeutic effects, CFF, EEG, VEP and psychometric tests are assessed weekly during the first month and every 4 weeks from the beginning of the second month until the end of the post-treatment follow-up.

Changes in the gut microbiome from antibiotic therapy with rifaximin alone or rifaximin with lactulose are analyzed comparing pre- and post-antibiotic time points. The follow-up data will show whether the change in the gut microbiome is persistent or transient. We will compare the effect of antibiotic therapy with rifaximin alone with a combination therapy with lactulose on the clinical course of MHE. As planned, NGS methods (Illumina sequencing, Illumina, San Diego, CA, USA) will be used to characterize the composition and changes of both stomach and small bowel microbiomes. Bacterial ribosomal ribonucleic acid (rRNA) will be isolated from aspirates, biopsies and feces and then stored in RNAlater at −80 °C. The samples will be analyzed by NGS methods as described below with the aim of identifying the microbiome of the stomach and the small bowel, as well as of the large bowel, in patients with liver cirrhosis and MHE and its changes before and after therapy (Fig. 1).

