### All subjects

Men and women in the age range 18–90 years at the time of enrollment and who are mentally competent, willing and able to understand the nature and risks of the proposed study, and able to sign the consent form prior to study entry. The individuals must have a projected life expectancy of 6 months or longer and must be able to comply with all study procedures and requirements. Women with childbearing potential must have a negative pregnancy test during the screening period. The diagnosis of liver cirrhosis is needed, established either by histology or by typical signs on transabdominal ultrasound in combination with signs of portal hypertension (ascites, enlarged spleen, fundic or esophageal varices), and the presence of MHE has to be confirmed. To confirm the diagnosis of MHE the following tests will be performed: number-connection test A (NCT-A), critical flicker frequency analysis (CFF), electroencephalography (EEG), and visual evoked potentials (VEP) whereby the final confirmation of MHE depends on the CFF result (CFF <39 Hz). The additional neurophysiological and neuropsychometric tests will be analyzed concerning diagnostic utility alone or in combination.

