
### Prior and concomitant medication

Patients may receive concomitant therapy during the study as required. Any concomitant medication at baseline as well as any changes made in concomitant medication within the study period (until the last follow-up examination) will be recorded in the electronic Case Report Form (eCRF). All concomitant therapy will be recorded using generic names. The necessity to use antibiotic therapy besides rifaximin leads to exclusion from this study.

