### Schedule of evaluations/Estimated timelines

This study consists of three phases: (1) the screening phase, (2) the treatment phase and (3) the follow-up phase (Table 1).

**Table 1 Tab1:** Clinical treatment plan

	Inclusion into study	Screening	Assignment to treatment group	Treatment phase	EOT	6 weeks after EOT	12 weeks after EOT = End of study
Time		Day −15 –day 0	0 (visit 0)	Days 1–90 (visits 1–3) −3d to +3d	Visit 3	Day 129– day 135 (visit 5) −3d to +3d	Day 171– day 177 (visit 6) −3d to +3d
Informed consent	x						
Demographics		X					
Medical history concomitant medication		X		x	X	x	X
Physical exam, vital signs, weight		X	x	x	X	x	X
ECG		X					
ECOG performance status and QOL assessment		X	x	x	X	x	X
Blood tests including pregnancy test		X	x	x	X	x	X
EGD with biopsies			x		X	x	X
	Inclusion into study	Screening	Assignment to treatment group	Treatment phase	EOT	6 weeks after EOT	12 weeks after EOT = End of study
Time		Day −15–day 0	0 (visit 0)	Days 1–90 (visits 1–3) −3d to +3d	Visit 3	Day 129– day 135 (visit 5) −3d to +3d	Day 171– day 177 (visit 6) −3d to +3d
*H. pylori* serology			x				
Stool samples			x	x	x	x	x
Rapid urease test			x				
Assessment of neurocognitive function (NCT-A, CFF, VEP, EEG)		X		Days 1–28 weekly, then every 4 weeks	>x	x	x

*CFF* critical flicker frequency, *ECG* electrocardiogram *ECOG* Eastern Cooperative Oncology group, *EEG* electroencephalogram, *EGD* esophagogastroduodenoscopy, *EOT* end of treatment, *NCT-A* number-connection test A, *QOL* quality of life, *VEP* visual evoked potentials

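### The stated adverse-event assessment ends at end of treatment, although two study-mandated endoscopies with biopsies come after it

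*Protocol article*

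**What the plan says.** The Safety assessment section opens with an explicit end point: "Patient safety will be assessed at every visit until the end of treatment". It goes on to say that adverse events (AEs) are monitored with NCI-CTCAE version 4.0, that all of them go into the eCRF, that serious events (SAEs) also go on a sponsor form, and that SAE processes are set out in a separate manual. None of these later sentences has a date of its own.

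Methods and design schedules upper endoscopy (EGD) at baseline and then "at the end of antibiotic treatment, as well as 6 and 12 weeks after the end of treatment to obtain gastric and duodenal biopsies". Table 1 repeats this. It gives the treatment phase as "Days 1–90 (visits 1–3"), places EOT at visit 3, and labels the final column "12 weeks after EOT = End of study".

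All subjects requires cirrhosis, shown either by histology or by ultrasound findings "in combination with signs of portal hypertension (ascites, enlarged spleen, fundic or esophageal varices"). Prior and concomitant medication sets a longer window for its own data: changes "within the study period (until the last follow-up examination) will be recorded".

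Statistical analysis compares laboratory variables and SAE rates between the arms in the safety set, with no time window stated.

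**The concern.** The stated safety window closes while the protocol still requires invasive procedures. The two follow-up endoscopies serve the microbiome objective. Their risk comes from taking part in the study, in a population where portal hypertension is common enough to be part of one diagnostic route. Someone following the Safety assessment section literally would not ask about AEs at the visits where these procedures take place.

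A second foreseeable event is progression to overt hepatic encephalopathy after treatment stops. The Background describes minimal encephalopathy as carrying a high potential for such progression. An episode after EOT would have no stated route into AE grading or, for an event not classed as serious, into any AE record.

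The Power analysis section says that the results are to support planning of a later multicenter trial. A gap in the AE record would carry forward into that planning, and events not asked about at the time are hard to recover.

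**Working it through.** The plan gives no figure for the length of its safety window, so there is none to reproduce. The check sets the sections side by side and does arithmetic on the visit schedule.

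**1. What continues after EOT, and what does not**

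| Item (source) | Treatment phase | EOT | 6 weeks after | 12 weeks after |
|---|---|---|---|---|
| EGD with biopsies (Table 1; the first is at visit 0) | no | yes | yes | yes |
| History, concomitant medication (Table 1) | yes | yes | yes | yes |
| Physical exam, vital signs, weight (Table 1) | yes | yes | yes | yes |
| ECOG status and quality of life (Table 1) | yes | yes | yes | yes |
| Blood tests (Table 1) | yes | yes | yes | yes |
| NCT-A, CFF, VEP, EEG (Table 1) | yes | yes | yes | yes |
| Safety/AE assessment (Safety assessment section) | yes | yes | not stated | not stated |

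Table 1 has no AE row, so the opening sentence of the Safety assessment section is the only place in the article that sets the window.

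**2. Do the visit days match the stated weeks?** Taking EOT as day 90:
- 6 weeks: 90 + 42 = day 132, the centre of the printed window of days 129–135.
- 12 weeks: 90 + 84 = day 174, the centre of the printed window of days 171–177.

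The schedule is consistent with itself, so the gap does not come from a misprinted day.

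**3. Share of study time after the window**
- Nominal: (174 − 90) / 174 = 84 / 174 = 48%.
- Earliest final visit: (171 − 90) / 171 = 81 / 171 = 47%.
- Latest final visit: (177 − 90) / 177 = 87 / 177 = 49%.

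**4. Share of endoscopies after the window** (the article says "RiMINI is a monocentric exploratory pilot study on 60 patients")
- Per patient: 4 EGDs, of which 2 come after EOT.
- All patients: 60 × 4 = 240 planned, and 60 × 2 = 120 after EOT, or 50%. This is an upper limit, because it assumes that nobody withdraws.
- The EOT endoscopy takes place at the last stated safety visit. Events on the day are caught, but delayed ones come after the window. The baseline endoscopy lies fully inside it.

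These are shares of exposure. They do not estimate how many events would be missed, and the document gives no complication rate from which to do so.

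**The case against.** The strongest reply is that much is still collected after EOT. Table 1 schedules history, examination, vital signs, blood tests and the full neurocognitive battery at both follow-up visits. Medication changes are recorded to the last visit, and CFF at end of follow-up is analysed. A reader might infer that off-treatment deterioration goes unrecorded; the documents contradict that. What stands is narrower: such deterioration is measured, but nothing says it is to be identified, graded and reported as an AE.

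The second reply is that only one sentence carries the end point. The instruction to document AEs and the planned SAE comparison have no cut-off, and the SAE manual is not shown. Serious endoscopic complications, or admission for overt encephalopathy, would normally be SAEs and might be covered there for longer. This stands as a limit on the claim: it cannot be said that serious events would be missed. It does not remove the point. Documentation depends on assessment, which the text ends at EOT, and a manual on SAE processes would not be expected to cover non-serious AEs. Nor is this a detail left out by a condensed article, because the article states the end point.

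Third, a reader might infer that the truncated window makes both arms and the procedures look safer than they are. This is not shown. The endoscopies are the same in both arms, study treatment has ended in both, and no mechanism for a biased comparison follows from the text. The primary efficacy result is unaffected.

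**Conclusion.** The point holds in a limited form. As written, safety assessment stops at EOT, while the protocol requires two further endoscopies with biopsies: half of those planned, up to 120 of 240, within the last 48% of study time (47–49% across the visit window). Delayed events of the EOT endoscopy are also outside it. AE identification, CTCAE grading and reporting have no stated coverage in follow-up, although the clinical, laboratory and neurocognitive data continue.

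This rests on three assumptions: EOT at day 90, all 60 patients completing (for the upper limit of 120), and the opening safety sentence governing the AE sentences that follow it. If practice or the SAE manual already runs to end of study, the defect is a wrong sentence in the article, which still needs correcting. Non-collection of serious events remains uncertain, and no bias between the arms is claimed.

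**What to change.** Reconcile the Safety assessment section with Methods and design, Prior and concomitant medication, and Table 1:

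- State that safety is assessed, and AEs and SAEs are collected, at every visit through the end of study (visit 6, 12 weeks after EOT).
- Check that the SAE manual gives the same end point.
- Report events in the safety set separately for the on-treatment and follow-up periods, with events related to an endoscopy identified as such.

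The cost is a short amendment, AE forms at two follow-up visits that already exist, and somewhat more AE entry. No visit, examination or procedure is added. Recruitment was under way at publication, so for any patient already past EOT, follow-up events would have to be sought from existing records.

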### Statistical analysis

All demographic and baseline variables are presented in descriptive statistics stratified by treatment arm in the full analysis set (FAS, all randomized patients). Exploratory tests, according to the level of the respective variables, will search for differences between both arms which might occur despite randomization. The primary target variable is compared between both treatment arms. The odds ratio for treatment success is calculated between both treatment arms together with the corresponding two-sided 95 % confidence interval. If the confidence interval is completely above or below the threshold of 1, the superiority of the corresponding treatment arm with larger success rates can be concluded. If the confidence interval covers the threshold of 1, then the lower and upper confidence limits give limits which can be used in non-inferiority statements. This analysis is performed primarily in the modified full analysis set (MFAS, all randomized patients but excluding those with missing CFF tests) according to the ITT principle. Missing values are imputed by the last observation carried forward principle.

Secondary analyses for the primary target variable include (1) logistic regression analysis with treatment arm, sex, age and baseline value of CFF as co-variables, (2) analog analyses in the per protocol set (PPS, patients of the MFAS excluding those with severe protocol violations), (3) analog analyses for the result of CFF at end of follow-up, (4) description of the results of the psychometric tests (mean and standard deviation) per treatment arm and comparison in two-sample *t* tests (both at end of treatment and end of follow-up).

The secondary efficacy variables are compared between the treatment arms in analysis of covariance (ANCOVA) models with treatment arm, sex, age and respective baseline variable as factors or co-variables, respectively.

Safety analysis is done in the safety set (SS, patients receiving at least one treatment) in descriptive and exploratory analyses. Laboratory variables and rates of SAEs are compared between both treatment arms using the Mann-Whitney *U* test and Fisher’s exact test.

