### Randomization procedure

The randomization will be performed with the clinical database software secuTrial that is also used for the data management in the study. The two arms will be randomized in a 1:1 ratio using the minimization method described by Pocock and Simon with a stratification for age and gender.

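### The primary odds ratio is unadjusted, although age and sex are minimization factors, baseline CFF is collected, and the adjusted model is already planned as secondary: an avoidable loss of efficiency

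*Protocol article*

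**What the plan says.** Under Statistical analysis, the protocol article defines the primary comparison: "The odds ratio for treatment success is calculated between both treatment arms", with a two-sided 95% CI and no covariates. The conclusion is tied to that interval: "If the confidence interval is completely above or below the threshold of 1, the superiority of the corresponding treatment arm" may be concluded; if it covers 1, its limits serve for non-inferiority statements.

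The same section lists, as the first secondary analysis of the primary variable, "logistic regression analysis with treatment arm, sex, age and baseline value of CFF as co-variables". The secondary efficacy variables are analysed by ANCOVA with arm, sex, age and the respective baseline value.

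Under Randomization procedure, allocation is 1:1, "using the minimization method described by Pocock and Simon with a stratification for age and gender". Entry requires a CFF below 39 Hz (All subjects), and Table 1 schedules CFF at screening, so every patient has a baseline value. The size is given under Methods and design: "RiMINI is a monocentric exploratory pilot study on 60 patients with MHE". Power analysis calls the trial an exploratory pilot that will inform a confirmatory trial, and concedes that only a drastic benefit of added lactulose could be shown.

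**The concern.** Age and gender were thought important enough to control at allocation, and baseline CFF important enough for the secondary model, yet the analysis that carries the conclusions uses none of them. The primary variable is thus analysed less efficiently than the secondary efficacy variables, and the article gives no reason.

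Two things are at stake. If the covariates predict success, a trial already short of information gives up power and risk-difference precision in its main answer. And because baseline CFF is not a minimization factor, a chance imbalance in it passes uncorrected into the primary result and into the planning of the confirmatory trial.

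**Working it through.** **Inputs from the article.** 60 patients, 1:1 (about 30 per arm); minimization on age and gender; two-sided 95% CI; baseline CFF below 39 Hz. No success rate, effect size, margin or correlation is given, so there is no stated figure to reproduce. Those values are assumptions below.

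**Step 1: how little information there is.** With equal observed success rates p, SE(log OR) = √(2 / (30·p·(1−p))).
- p = 0.5: SE = √(2/7.5) = 0.516; CI = exp(±1.96 × 0.516) = 0.36 to 2.75.
- p = 0.3 or 0.7: SE = √(2/6.3) = 0.563; CI = 0.33 to 3.02.

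With 30 per arm, 80% power needs roughly 50% versus 83.5% success (OR 5.1). A 20-point difference has about 34% to 39% power. This agrees with the article's own caution.

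**Step 2: chance imbalance in baseline CFF.** The between-arm difference in baseline means has standard error √(2/30) = 0.26 SD. With baseline correlation r, a one-standard-error imbalance shifts the outcome by r × 0.26 SD, which is 0.18 SD at r = 0.7 and nothing at r = 0.

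**Step 3: adjustment on the odds-ratio scale.** About 2,000 simulated trials per row, 60 patients, minimization on dichotomized age and sex, 50% success in the reference arm, 0.8 SD effect. The columns give mean log OR (mean SE), their ratio, and power.

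| Correlation: baseline / age-sex | Crude | Ratio | Power | Adjusted | Ratio | Power |
|---|---|---|---|---|---|---|
| 0 / 0 | 1.38 (0.599) | 2.30 | 65% | 1.47 (0.634) | 2.32 | 65% |
| 0.3 / 0.2 | 1.37 (0.600) | 2.28 | 64% | 1.60 (0.677) | 2.36 | 68% |
| 0.5 / 0.3 | 1.39 (0.602) | 2.31 | 66% | 1.94 (0.782) | 2.48 | 75% |
| 0.7 / 0.3 | 1.35 (0.600) | 2.25 | 64% | 2.56 (0.999) | 2.56 | 82% |

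The adjusted SE is larger in every row. Power rises only because the conditional odds ratio moves further from 1 than its SE grows. With no effect, the crude test rejected in 3.3% to 5.9% of trials (Monte Carlo error about 1 point).

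**Step 4: adjustment on the marginal scale.** The standardized risk difference is (1/N) Σ [p̂(arm 1, xᵢ) − p̂(arm 0, xᵢ)], with p̂ from the logistic model. Simulation of 60 patients, baseline truncated below 39 Hz, 0.7 SD effect:

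| Baseline correlation | Power, crude | Power, adjusted | Variance, standardized versus crude risk difference |
|---|---|---|---|
| 0 | 54% | 56% | +2% |
| 0.3 | 52% | 57% | −4% |
| 0.5 | 53% | 61% | −16% |
| 0.7 | 50% | 69% | −33% |

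The two risk differences have the same mean (within 0.002). A separate run under the same assumptions gave 50–54% crude against 56–68% adjusted power, a variance change of +3% to −31%, and type I error of 4–6%; its range is the one used here. In patient numbers, 60/1.03 ≈ 58 at worst and 60/0.69 ≈ 87 at best.

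**The case against.** The strongest case against has four parts.

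- **The adjusted analysis is already prespecified.** True: the same variable and exactly these covariates. A reader might infer that the plan throws the baseline data away; it does not. What remains is which result carries the conclusion. In an open-label trial with two analyses that may disagree, that order should favour the more efficient one.
- **Adjustment widens the odds-ratio interval.** Also true. A reader might infer that the crude interval is too wide and that adjustment would narrow it; Step 3 shows the reverse. It matters for the non-inferiority statements: with truly equal arms, the median upper limit was about 2.8 crude and 3.0 to 4.1 adjusted. The estimand changes too: at a 0.6 SD effect and baseline correlation 0.7, the median odds ratio was 2.6 crude and 5.7 adjusted. Simply putting the conditional odds ratio in the primary place would therefore be a poor remedy; a marginal estimate is needed.
- **The gain rests on a correlation that the article does not give.** This stands. The gain is near zero if baseline CFF, age and sex predict little.
- **It is an exploratory pilot.** This limits the weight of the point but does not remove it, since the results are meant to plan the next trial.

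Two further inferences should be resisted. Unadjusted analysis after minimization did not inflate type I error here. And the article does not spell out how success is defined: that it is a dichotomized CFF is only inferred from the analysis set being defined by CFF tests. ANCOVA on CFF in Hz gave higher power still (77% to 97% in the Step 4 scenarios), but that measures a different change, not the benefit of adjusting the primary model.

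**Conclusion.** The point holds as one of efficiency. The crude primary test is valid. Compared with the model already planned as secondary, it forgoes about 2 to 18 points of power, and the variance of the risk difference would change by +3% to −31% with adjustment. These figures assume 60 evaluable patients, a 0.7 SD effect, a baseline correlation from 0 to 0.7 and a success rate near one half in the reference arm; none of these assumed values apart from the 60 patients is in the article. If the covariates are not prognostic, almost nothing is lost by adjusting; if they are, the gain is worth having in a trial of this size. Independently of power, the primary result as planned does not correct for a chance imbalance in baseline CFF. The change should be made, but the results would not be wrong without it.

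**What to change.** - Make the planned logistic model (arm, sex, age, baseline CFF) the primary analysis.
- Report from it a covariate-standardized risk difference, or a marginal odds ratio, with a 95% CI. Base the superiority and non-inferiority statements on that estimate; the no-difference threshold is 0 for a risk difference and stays 1 for a marginal odds ratio.
- Keep the crude odds ratio as a supportive analysis. If the conditional odds ratio is reported, label it as such and state that it lies further from 1, with a wider interval. That is the main downside of the change.
- If success is defined from CFF, add an ANCOVA of end-of-treatment CFF in Hz with the same covariates as a supportive analysis.

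The cost is wording in the protocol or analysis plan. No new data, visits or patients are needed.

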### Rationale for the explorative study

Continuous therapy with rifaximin in combination with lactulose significantly reduces the risk of overt HE, recurrence and HE-related hospitalization in randomized double-blind placebo-controlled clinical trials [1–3]. Rifaximin is approved for the therapy of *overt* HE in Germany. Therapy with lactulose has been shown to improve cognitive functions in patients with liver cirrhosis. So far, whether monotherapy with rifaximin is as effective as combination therapy with rifaximin and lactulose in the treatment of MHE, has not been addressed in a prospective clinical trial.

Rifaximin is a minimally absorbed gut-selective antibiotic and thus impacts on the intestinal microbiome. The role of the intestinal microbiome in the pathophysiology of HE is still little understood. To our knowledge, changes in the microbiome of the upper gastrointestinal (GI) tract as result of therapy with rifaximin have not yet been addressed in clinical studies and studies addressing the persistence of changes of the intestinal microbiome are scarce [19].

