### Power analysis

This is an exploratory pilot study as so far data on the monotherapeutic effect of rifaximin in the treatment of MHE are scarce. The results will give the basis for planning a later confirmatory multicenter trial. With the given sample sizes the proof of differences between the two treatment options, or of acceptable non-inferiority margins, can be expected only if the additional of lactulose drastically improves the success rates of the rifaximin treatment.

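### When the odds-ratio interval covers 1, the plan lets the observed confidence limits feed non-inferiority statements, with no margin, direction or acceptability criterion fixed in advance

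*Protocol article*

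**What the plan says.** The Statistical analysis section sets out two branches for the primary target variable.

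- **Measure:** "The odds ratio for treatment success is calculated between both treatment arms", with the "corresponding two-sided 95 % confidence interval".
- **Interval excludes 1:** "If the confidence interval is completely above or below the threshold of 1, the superiority of the corresponding treatment arm" with the larger success rate can be concluded.
- **Interval covers 1:** "then the lower and upper confidence limits give limits which can be used in non-inferiority statements".

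No numerical margin appears, and the section does not say which arm is the reference for non-inferiority. The Power analysis section returns to the subject. It says that, at the given sample size, proof of differences "or of acceptable non-inferiority margins, can be expected only if" adding lactulose improves success rates drastically. It does not say what makes a margin acceptable.

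Two further places give the context. The rationale names as unanswered "whether monotherapy with rifaximin is as effective as combination therapy with rifaximin and lactulose in the treatment of MHE". Methods and design states that "RiMINI is a monocentric exploratory pilot study on 60 patients with MHE", and the Power analysis section says that the results are meant as the basis for planning a later confirmatory multicentre trial.

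**The concern.** A non-inferiority claim is a test against a margin chosen for clinical reasons before the data are known. In this plan the branch opens because the superiority comparison was not significant, and the only limit it offers comes from the same interval. If a report then calls that limit acceptable, the criterion has been fitted to the result.

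The gap is not one that a separate analysis plan would simply fill. The article itself says where the limits come from, so setting a margin in advance would change the rule.

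The interpretation of the comparison is at stake. The rationale's question about monotherapy and combination is one that readers will want answered. The Power analysis section itself expects proof only if lactulose has a drastic effect, so an interval covering 1 is a likely outcome. The wording leaves room to present that outcome as evidence that monotherapy is good enough.

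**Working it through.** **Inputs.** From the article: 60 patients, 1:1 allocation (so 30 per arm), an odds ratio and a two-sided 95% interval. The article gives no success rates, power or margin, so the figure of 60 cannot be reproduced. All success rates and margins below are assumptions. The odds ratio is rifaximin alone against the combination, so values below 1 mean that monotherapy is worse. Intervals are Wald intervals on the log odds ratio, with 0.5 added to every cell if any cell is zero.

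**Step 1. Width of the interval when the observed rates are equal.** With a successes and b failures in each arm, SE(log OR) = √(2/a + 2/b).

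- At 50% (a = b = 15), SE = √(4/15) = 0.516 and exp(±1.96 × 0.516) = 0.36 to 2.75. If the combination succeeds in 50%, its odds are 1. Odds of 0.363 correspond to 0.363/1.363 = 27%.
- At 70% (a = 21, b = 9), SE = √(2/21 + 2/9) = 0.563 and exp(±1.96 × 0.563) = 0.33 to 3.02. Odds of (0.7/0.3) × 0.331 = 0.773 correspond to 0.773/1.773 = 44%.

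Even with no observed difference, the data would be compatible with monotherapy being 23 points (50 to 27) or 26 points (70 to 44) worse.

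**Step 2. How often the interval covers 1.** This sums exact probabilities over two independent binomials with n = 30.

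| True success, monotherapy vs combination | Interval covers 1 |
|---|---|
| 50% vs 50% | 95% |
| 50% vs 60% | 88% |
| 50% vs 70% | 65% |
| 50% vs 80% | 32% |

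Among the trials at 50% vs 70% whose interval covers 1, the median lower limit is 0.18. These percentages say how often the branch is entered. They are essentially the complement of superiority power (0.35 by formula at 50% vs 70%).

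**Step 3. Is the bare statement about the limit wrong too often?** Take the statement that monotherapy is not worse than the observed lower limit L. It is false when L lies above the true odds ratio.

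| True success, monotherapy vs combination | Interval covers 1 and L is above the true OR | Same, among trials covering 1 |
|---|---|---|
| 50% vs 60% | 2.2% | 2.5% |
| 50% vs 70% | 2.2% | 3.4% |
| 50% vs 80% | 2.6% | 8.2% |
| 70% vs 90% | 2.5% | 4.5% |

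Read as an estimate, the limit therefore has about the one-sided 2.5% error expected of it, and somewhat more after conditioning on entry to the branch. The problem arises only in the further step from not worse than L to non-inferior.

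**Step 4. What a margin fixed in advance would do at this size.** The table gives the chance that the lower limit exceeds an assumed odds-ratio margin when the arms are truly equal.

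| Margin | Both 50% | Both 70% |
|---|---|---|
| 0.50 | 26% | 24% |
| 0.33 | 55% | 51% |
| 0.25 | 74% | 68% |

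For a risk-difference margin m and equal rates p, n per arm = (1.96 + 0.84)² × 2p(1 − p)/m². With 80% power and one-sided 2.5%, rates of 50% to 80% need 393 to 252 per arm for 10 points, 99 to 63 for 20 points and 44 to 28 for 30 points. The trial has 30.

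**The case against.** The strongest case for the plan is that it declares nothing. The superiority branch says that a conclusion can be drawn. The other branch says only that the limits can be used, and the natural reading in a pilot is estimation: report which differences are excluded and carry them into the next trial. The phrase "or of acceptable non-inferiority margins" implies that a limit may be found unacceptable. The stated primary objective is to analyse efficacy in the two arms, without a non-inferiority hypothesis, and the sentence in the rationale describes a gap in the literature.

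Much of this stands, and it rules out three stronger readings that a reader might infer.

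- **Non-inferiority can never fail.** This would follow only if the observed limit were itself the margin. The article does not say that, and the word acceptable points the other way.
- **The rule has no error control.** Step 3 shows that the bare statement about the lower limit is false in only about 2.2% to 2.6% of trials. Control is lost when the limit is judged acceptable after it has been seen.
- **65% of trials would wrongly claim non-inferiority at 50% vs 70%.** That figure is the chance of an inconclusive superiority comparison under assumed rates.

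The objection does not remove the gap. The text speaks of non-inferiority statements, beside a superiority rule worded as a conclusion, and gives no criterion for an acceptable limit. Nothing in the article bars the later judgement. The direction is also unclear: the Power analysis section ties acceptable margins to a drastic lactulose benefit, but such a benefit would make non-inferiority of rifaximin alone harder to show.

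**Conclusion.** The point holds in a limited form. The article lets a non-significant result feed non-inferiority statements whose limits are the observed ones, and fixes no margin, direction or criterion of acceptability. Reporting the limits is sound. A claim that monotherapy is non-inferior would rest on a judgement made after the data are seen.

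The room for such a judgement is large: with 30 per arm and equal observed rates, the lower limit would be about 0.33 to 0.36 for assumed rates of 50% or 70%. These sizes rest on the assumed success rates, on Wald intervals and on all 60 patients being analysed. Patients excluded for missing flicker-frequency tests would widen the intervals.

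Severity is moderate to low, because the trial is declared exploratory and is meant to inform a confirmatory one.

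**What to change.** Replace the sentence on non-inferiority in the Statistical analysis section with: *If the interval covers 1 the result is inconclusive; the OR with its 95% CI is reported as an estimate for planning the confirmatory trial, and no non-inferiority claim is made.* Bring the Power analysis section into line by removing its reference to acceptable non-inferiority margins.

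If a non-inferiority statement is wanted, fix and justify one margin, its scale and its direction (rifaximin alone against the combination) before any comparative look at the data. Claim non-inferiority only if the confidence interval excludes that margin, and state in the Power analysis section how likely that is with 30 per arm.

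The cost is a short wording amendment, with no new patients or procedures. The first option gives up a claim that the trial's size is unlikely to support. The second keeps the claim, but it would often fail at this size even if the arms are truly equal, unless the margin is very wide.
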